## Abstract

**Aims:**

Using thermal-based energy sources [radiofrequency (RF) energy/cryo energy] for catheter ablation is considered effective and safe when performing pulmonary vein isolation (PVI) in patients with paroxysmal atrial fibrillation (AF). However, treatment success remains limited and complications can occur due to the propagation of thermal energy into non-target tissues. We aim to compare pulsed field ablation (PFA) with RF ablation in terms of efficacy and safety for patients with drug-resistant paroxysmal AF.

**Methods and results:**

The BEAT PAROX-AF trial is a European multicentre, superiority, open-label randomized clinical trial in two parallel groups. A total of 292 participants were recruited in 9 high-volume European clinical centres in 5 countries. Patients with paroxysmal AF were randomized to PFA (FARAPULSE Endocardial Ablation System©, Boston Scientific) or RF using the CLOSE protocol with contact force sensing catheter (SmartTouch© catheter and CARTO© Biosense Webster). The primary endpoint will be the 1-year recurrence of atrial arrhythmia, and the major secondary safety endpoint will be the occurrence of acute (<7 days) procedure-related serious adverse events, or pulmonary vein stenosis, or atrio-oesophageal fistula up to 12 months. Additionally, five sub-studies investigate the effect of PFA on oesophageal safety, cerebral lesions, cardiac autonomic nervous system, durability of PVI as assessed during redo ablation procedures, and atrial and ventricular function. The study began on 27 December 2021 and concluded recruitment on 17 January 2024. Results will be available in mid-2025.

**Conclusion:**

The BEAT PAROX-AF trial aims to provide critical insights into the optimal treatment approach for patients with paroxysmal AF.

## Introduction

Performing catheter ablation has emerged as a well-excepted therapeutic approach for the treatment of patients with symptomatic paroxysmal atrial fibrillation (AF).^1–3^ Thermal-based energy sources [radiofrequency (RF) energy/cryo energy] for catheter ablation are considered effective and reasonably safe in this indication.^2,4^ However, treatment success remains limited with single-procedure success rates between 60% and 80%.^5–8^ Pulmonary vein reconnection is believed to be a main underlying factor limiting treatment success. Therefore, creating more durable lesions when performing catheter ablation has been a major focus of scientific investigation within the field of clinical electrophysiology over the last decade.^9,10^ Furthermore, thermal ablation strategies can result in rare yet significant complications since these methods ablate all types of tissue in a non-selective manner.^11–13^ Pulsed field ablation (PFA) is a novel, non-thermal ablation strategy based on pulsed electric field (PEF) energy delivery. This energy source allows highly selective cardiac ablation that resulted in safe, durable, and transmural lesions as demonstrated in smaller studies.^14,15^ The BEAT PAROX-AF trial aims to provide comparative evidence of PEF vs. RF ablation in terms of efficacy and safety when treating patients with paroxysmal AF. The primary objective of the trial is to test the superiority of PFA over standard RF catheter ablation on the rate of 1-year recurrence of atrial arrhythmia. We hypothesize that PEF energy, a non-thermal ablative modality highly specific for cardiac cells, will deliver more durable PVI than RF energy, translating into superior clinical outcomes for PFA as compared with RF energy. By evaluating the outcomes of PFA, the study aims to provide critical insights into the optimal treatment approach for paroxysmal AF, to improve their clinical outcomes, including quality of life, and procedural duration.

## Methods

### Study design, setting, and recruitment

The BEAT PAROX-AF trial is a European multicentre, prospective, superiority, open-label randomized clinical trial with two parallel groups (PEF vs. RF catheter ablation). The study protocol is registered on clinicaltrials.gov (NCT05159492) and has been approved by the local ethics committee for all participating centres. The present report adheres to the SPIRIT 2013 Statement.^16^ Participants were recruited in nine high-volume European clinical centres in five countries (France, Czechia, Germany, Austria, and Belgium*)* (see Supplementary material for details on all participating centres). All centres have extensive experience in performing both types of ablation strategies. To attenuate the learning effect in PVI using PFA, participating centres started enrolling in the BEAT PAROX-AF trial after at least three PFA with study devices, either in clinical routine practice or during the study-specific training period. Six of the centres perform ∼600 AF ablations annually, while the rest do over 300 cases per year.

### Study population

Patients aged ≥18 and ≤80 years with drug-resistant and documented symptomatic paroxysmal AF, indication for AF ablation, and effective oral anticoagulation >3 weeks before the planned ablation procedure were eligible for inclusion. Main exclusion criteria were persistent AF, paroxysmal AF secondary to electrolyte imbalance, thyroid disease, alcohol or other reversible/non-cardiac causes, left atrial (LA) anteroposterior diameter ≥ 5.5 cm, or any prior atrial endocardial or epicardial ablation procedure except for the ablation of cavotricuspid isthmus (CTI)-dependent flutter or right-sided supraventricular tachycardia, PV abnormality, stenosis or stenting, and refusal to give informed consent. Detailed eligibility criteria are listed in the Supplementary material.

### Interventions

In both groups, patients were under conscious sedation (benzodiazepine, morphine), and boluses of propofol were injected just before energy deliveries. General anaesthesia, including intubation, was not used. Procedures will include transseptal puncture in the absence of foramen ovale.

### Pulmonary vein isolation using pulsed field ablation

Through the precise and momentary creation of a therapeutic electric field, PFA treats the uniquely sensitive myocardium (*Figure 1D*). Collateral, non-target tissues are spared due to their higher threshold to PEF.^15,17^ The FARAPULSE Endocardial Ablation System (Boston Scientific©) includes the FARAWAVE Endocardial Ablation Catheter System, the FARASTAR Endocardial Generator System, and the FARADRIVE Deflectable Sheath System (*Figure 1*). The 12 F over-the-wire PFA catheter has five splines that each contain four electrodes and can be deployed in either a basket (*Figure 1A*) or a flower configuration (*Figure 1B*). The catheter is advanced over a guidewire such that the splines achieve circumferential contact/proximity with the PV antra (*Figure* *1B* and *C*). The ablative energy is delivered from all electrodes. The catheter is rotated between applications to ensure circumferential PV ostial and antral coverage. Energy (2000 V) was delivered at least eight times per vein with two different catheter configurations and rotations (flower and basket configuration). Before starting ablation, activated clotting time is aimed to be above 300 s. After performing a transseptal puncture, all four PVs were isolated, demonstrated by an entrance and/or exit block. If subjects have a history of typical flutter or have an inducible typical flutter, they underwent CTI interruption using RF. Ablation of an accessory pathway, atrioventricular nodal re-entrant tachycardia, treatment of incidental left-sided atrial flutter, or incessant atrial tachycardia may be performed at the investigator’s discretion if required for subject welfare, using RF and not PEF. During the index procedure for paroxysmal AF, no other lesions were attempted.

**Figure 1 euae103-F1:**
[figure not shown]
Performing pulmonary vein isolation with the FARAPULSE© PFA system.

### Pulmonary vein isolation using contact force radiofrequency

The utilization of RF energy to perform PVI is a widely accepted treatment option and continues to be the current ‘gold standard’ when performing catheter ablation procedures. To do so, the CARTO© (Biosense Webster) platform was used along with a contact force catheter (SmartTouch or SmartTouch Surround Flow), to achieve an ablation index value of 300–400 and at least 500 at the posterior and anterior segments of PV antra, respectively. Power was restricted to 35/45 W with a distance of 6 mm or less between consecutive RF deliveries in accordance with the CLOSE protocol.^18^ Pulmonary vein isolation demonstrated by the entrance and/or exit block was the endpoint of the procedure.

### Redo procedure

If redo procedures are needed, they will be performed using RF in both groups as described above. Pulmonary vein reconnections, lesion set, and arrhythmia mechanism (if applicable) will be documented. This will potentially require the alcoholization of the vein of Marshall and the creation of a mitral isthmus line or any other clinically relevant ablation strategy.

## Endpoints

### Primary endpoint

The primary efficacy endpoint was defined as the proportion of subjects experiencing 1-year single-procedure clinical success, defined as per the 2017 Heart Rhythm Society (HRS) consensus statement: successful index AF ablation, absence of atrial arrhythmia recurrence ≥30 s on any type of recording [transtelephonic monitoring (TTM), Holter recording, 12-lead electrocardiogram (ECG), rhythm strip, or other diagnostic ECG documentation], absence of use of class I or III antiarrhythmic drugs (AAD) except for non-atrial arrhythmia, and absence of redo ablation (except for typical flutter), in the 12 months following the index ablation procedure.^4^ A blanking period of 60 days for arrhythmia recurrence after the index ablation procedure will be systematically used, as is usual in AF ablation.^19^ Recurrences of atrial arrhythmia during the blanking period will not be considered in the determination of the primary endpoint. However, any redo ablation for atrial arrhythmia except for typical flutter performed during or after the blanking period will be considered a failure.

### Secondary endpoints

Secondary efficacy endpoints are as follows:

The proportion of subjects with 1-year multiple-procedure success defined as:Absence of atrial arrhythmia recurrence ≥30 s on any type of recording as defined aboveAbsence of use of class I or III AAD (except for non-atrial arrhythmia)
Improvement in quality of life, using a standard set of patient-reported questionnaires for paroxysmal AF already validated in the different native languages of the participating centres^20^: general health-related quality of life (physical and mental components of the SF-12 score measured at 6 and 12 months^21^) and AF-related quality of life assessed with the Atrial Fibrillation Effect on QualiTy-of-life (AFEQT) questionnaire at 6 and 12 months.^22^ The AFEQT is composed of 20 items covering 4 individual domains: symptoms (4 items), daily activities (8 items), treatment concern (6 items), and treatment satisfaction (2 items). The AFEQT global score (using the first three domains as recommended) and scores for each of the three subdomains (symptoms, daily activities, and treatment concern) will be measured.Proportion of participants with death, strokes, or embolic events from arrhythmia up to 12 months after the index ablation procedure.

The secondary safety endpoint is the proportion of participants with one or more of the following ablation procedure-related serious adverse events (SAE), as adjudicated by a blinded Clinical Event Committee:

Early-onset SAE (within 7 days of index ablation procedure): death, myocardial infarction, persistent diaphragmatic paralysis, stroke, transient ischaemic attack (TIA), peripheral or organ thromboembolism, cardiac tamponade or perforation, pericarditis, new hospitalization (excluding those solely due to arrhythmia recurrence), prolonged index hospitalization, heart block, or vascular access complications.Late-onset SAE (at any time through 12-month follow-up): PV stenosis or atrio-oesophageal fistula.

Other secondary endpoints are the duration of the AF ablation procedure (mean total procedure duration, LA dwell time, mean fluoroscopy time) and 1-year healthcare resource utilization (all-cause hospitalizations, AF-related and non–AF-related cardiovascular hospitalizations, repeat ablations, direct current cardioversions). Among exploratory endpoints belong the change in mean PV diameter from baseline to 2 months after the index ablation and the impact of ablation on the indices of cardiac autonomic regulations.

### Study schedule

The study schedule is summarized in *Table 1*.

**Table 1 euae103-T1:** Study schedule summary for the BEAT PAROX-AF trial and sub-studies

Assessment	Screening visit^a^	Baseline visit^a^	Index ablation procedure	Pre-discharge visit		1-Month phone call	2-Month visit	Redo procedure (if needed)	6-Month visit	12-Month visit	Unscheduled visit
	−2 months to D-1	D-1 to D0	D0	D1	D1 to D3	D30 (±7)	D60 (±15)	D60 to D365	D180 (±30)	D365 (±30)	
Eligibility criteria	X	X									
Informed consent	X	X									
CT/TEE to exclude LA thrombus		X									
Randomization		X^b^									
Procedure characteristics			PEF or RF					RF only			
AAD and anticoagulant medications	X	X		X		X	X		X	X	X
Recurrent arrhythmia, cardioversions, hospitalizations				X		X	X		X	X	X
12-lead ECG		X		X			X		X	X	X
24 h Holter							X		X	X	
Transtelephonic ECG monitoring					Weekly and in case of symptoms						
Cardiac CT/MRI		X					X				
TTE		X								X	
NYHA classification		X		X		X	X		X	X	X
Fluoroscopic examination of the diaphragm			X				X^c^		X^c^	X^c^	
QoL questionnaires		X							X	X	
Adverse events		X	X	X		X	X	X	X	X	X
Sub-study examinations											
Oesophagoscopy					X						
Brain MRI					X		X^d^				
24 h Holter		X									
Extracardiac vagal stimulation			X								
Atropine test		X		X					X	X	
CARTO export			X					X			
Cardiac MRI		X	X				X				

AAD, antiarrhythmic drug; CT, computed tomography; LA, left atrial; MRI, magnetic resonance imaging; NYHA, New York Heart Association; PEF, pulsed electric field; QoL, quality of life; RF, radiofrequency; TEE, transoesophageal echocardiography; TTE, transthoracic echocardiography.

^a^The screening visit and the baseline visit could be done the same day.

^b^Randomization may be performed up to 10 days before Day 0 if required for ablation scheduling.

^c^If the procedural examination indicates decreased phrenic nerve function.

^d^For participants with cerebral lesions on baseline brain MRI.

### Screening

Patients scheduled for AF consultation or ablation were screened in the cardiac electrophysiology departments. The documentation of eligibility criteria required the collection of data from the patient’s medical history, transthoracic echocardiography (TTE) and cardiac CT, or magnetic resonance imaging (MRI) results. Eligible patients willing to participate after reading the information sheet were asked to give written informed consent witnessed by a principal or co-investigator.

### Randomization and allocation concealment

The randomization list was established by the biostatistician of the EUCLID platform (CHU Bordeaux) before the start of the trial and kept confidential in a secure environment. Randomization was balanced (1:1 ratio) and stratified by centre. Full details of the randomization scheme were not disclosed to ensure allocation concealment and were included in a separate document with restricted access, kept by the biostatistician. Participants were included during pre-operative consultation, and eligible patients were randomized preferentially the day before or the day of the procedure or up to a maximum of 10 days in advance to facilitate ablation scheduling. Randomization was conducted through the trial electronic case report form (eCRF), after documentation of the eligibility criteria. The assigned intervention was communicated to participants on-site before the AF ablation procedure to minimize the likelihood of withdrawals between randomization and intervention.

### Blinding

Due to the nature of the intervention and important differences between PFA and RFA, the blinding of patients and clinical staff is not possible. However, a centralized assessment (brain MRI, cardiac MRI, video-recording of oesophagoscopy, Holter, TTM) is performed blinded to allocated intervention whenever possible, to limit the probability of differential evaluation between the two groups.

### Follow-up visits

Patients will be followed with a phone call at 1 month and outpatient visits at 2 months, 6 months, and 12 months. At each in-hospital visit, medication, symptoms of arrhythmia, and adverse events will be collected, a physical examination will be performed, and a 12-lead ECG, as well as a 24 h Holter monitor recording, will be obtained. Furthermore, self-performed single-lead ECGs will be conducted weekly and in case of symptoms via a smartphone application and then sent to the clinical centre for day-to-day care and to the centralized core lab for further evaluation. A fluoroscopic examination of diaphragm motion will be performed during follow-up if the procedural examination indicated phrenic nerve damage. All patients will undergo cardiac computed tomography (CT) or cardiac MRI at the 2-month follow-up to assess PV stenosis. Computed tomography protocols will consist of a conventional arterial-enhanced ECG-gated acquisition. Magnetic resonance imaging protocols will consist of a three-dimensional angiography acquisition with respiratory navigation. The diameter analysis of all PVs will be centralized by a core lab at the University of Bordeaux. SF-12 and AFEQT will be collected at the 6-month and 12-month follow-up visits, and a TTE will be performed at 12 months. A redo procedure will be collected, as well as any unscheduled visit for AF.

### Sample size

Radiofrequency has been reported to provide around 65% single-procedure success rate in paroxysmal AF.^23,24^ A success rate of 80% could be expected with PEF.^25^ With a type I error rate of 5%, a power of 80%, and randomization with a 1:1 ratio, we need to include 276 participants (138 participants in each arm). After accounting for a maximum of 5% of missing data at 12 months, the total sample size was increased to 292 participants (146 participants in each arm).

### Statistical methods

Primary analyses will be conducted according to the intention-to-treat principle, in which all randomized patients will be included in the arm in which they first were randomized, and all their data will be used. The comparisons of the single-procedure 1-year success rates between the PEF arm and the RF arm will use logistic mixed models with a random effect on the study centres and fixed effects on the procedure arms, with a two-sided type I error rate of 5%. The model will be adjusted on major prognostic factors (common ostia, intermediate PV, PV diameter > 25 mm, and body mass index). For secondary objectives, linear (for quantitative outcomes) and logistic (for binary outcomes) mixed models will be used to compare the outcomes between the arms. The assumption of the models will be systematically checked.

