### Protocol amendments

Since the first approved version of the protocol (version 1.0 of 13 September 2021), several protocol amendments were made. Major changes were related to eligibility criteria (documentation of paroxysmal AF, documentation of LA diameter and LV ejection fraction, contraception, formalization of the indication for PVI/AF ablation), study examination and randomization timeframes to resolve scheduling difficulties, precisions on the investigational procedure and redo procedures, and authorized treatments and procedures. The currently approved version is version 7.0 of 19 June 2023.

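### The primary model omits baseline class I/III antiarrhythmic drug use, which the trial records and which is the pre-randomisation counterpart of a failure component; adding it is a cheap, optional gain in efficiency

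*Protocol article*

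**What the plan says.** The Statistical methods section compares one-year single-procedure success with "logistic mixed models with a random effect on the study centres and fixed effects on the procedure arms", at a two-sided 5% level. It then names the covariates: "The model will be adjusted on major prognostic factors (common ostia, intermediate PV", followed by a PV diameter above 25 mm and body mass index. That is three indicators of pulmonary vein anatomy plus body mass index. Nothing in the list describes drug treatment at entry.

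The Primary endpoint section requires, among other conditions, "absence of use of class I or III antiarrhythmic drugs (AAD) except for non-atrial arrhythmia" over the 12 months after the index ablation. The 60-day blanking period is stated for arrhythmia recurrence. The article states none for drug use.

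In Table 1 (Study schedule), the row "AAD and anticoagulant medications" is marked at both the screening and the baseline visit, so the variable exists for every participant. Under Randomization and allocation concealment, centre is the only stratification factor.

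**The concern.** A patient who enters the trial on a class I/III drug and is still taking it for atrial arrhythmia after ablation fails the endpoint as written, whatever the rhythm recordings show. Of the variables recorded before randomisation, baseline use is therefore the one most directly tied to a component of the endpoint, and the tie can be seen in the article itself.

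Neither the randomisation nor the model balances it. A chance difference between arms in baseline use would carry into the crude and the adjusted treatment effect, and a correction made after the results are known would carry less weight. If the factor is strongly prognostic, some power is also left unused.

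**Working it through.** **1. The plan's own figure.** Inputs from the Sample size section: success 65% with radiofrequency, 80% with pulsed field ablation, 5% type I error, 80% power, 1:1 allocation, 5% missing data. The two-sided level comes from Statistical methods. With pooled variance and no continuity correction:

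n per arm = [1.96·√(2·0.725·0.275) + 0.842·√(0.65·0.35 + 0.80·0.20)]² / 0.15² = (1.238 + 0.524)² / 0.0225 ≈ 138.

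Then 138 / 0.95 = 145.3, rounded up to 146. Both stated figures (276 and 292) reproduce. Power is 80.0% at 138 per arm and 82.2% at 146. This is an unadjusted comparison of two proportions, so the stated power relies on no covariate.

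**2. Size of a chance imbalance.** The article does not give the proportion on a class I/III drug at baseline, so 30% to 70% is assumed. The 95% limit for the between-arm difference is 1.96·√(2q(1−q)/146):

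- q = 50%: 1.96 × 5.9 points = 11.5 points
- q = 30% or 70%: 10.5 points

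**3. What that does to the success difference.** Strength is also assumed. For each odds ratio for failure, the success rates on and off drug are set so that overall success is 65%. Their difference is multiplied by the limit in step 2.

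| Assumed odds ratio for failure | Success difference, off minus on drug | Shift at the 95% limit |
|---|---|---|
| 1.5 | 8.8 to 9.3 points | 0.9 to 1.0 points |
| 2 | 14.9 to 16.2 points | 1.6 to 1.8 points |
| 3 | 22.6 to 25.9 points | 2.4 to 2.8 points |
| 5 | 30.5 to 37.2 points | 3.2 to 3.9 points |

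Ranges run over q = 30%, 50% and 70%. Example: q = 50%, odds ratio 3 gives 0.244 × 0.1147 = 2.8 points.

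**4. Power with and without the term.** Trials were simulated at marginal success of 65% and 80%. With the four planned covariates in both models, adding baseline drug use gives no gain at an odds ratio of 2 or less, about 2 points at 3 and about 5 points at 5. The type I error stays near 5% throughout. A simpler run with 138 per arm and drug use as the only covariate, at an odds ratio of 5, moves power from 80.5% to 84.6% (q = 30%), 79.6% to 83.8% (50%) and 81.7% to 84.1% (70%), which is gains of 4.2, 4.2 and 2.4 points before rounding to one decimal place.

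**5. Room in the model.** Expected failures are 292 × (0.35 + 0.20)/2 = 80. The planned model has five fixed terms besides the intercept (arm and four covariates). One more makes six, or 80/6 ≈ 13 failures per term.

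**The case against.** The choice of prognostic covariates is a judgement. This plan made it in advance, and nothing in the article contradicts it. Four points on that side stand.

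- **Only use after ablation is a failure component.** A reader might infer that baseline use is itself part of the endpoint. It is not. The article does not say how often a drug is continued, and the drug-resistant eligibility criterion does not say who is still taking one at entry.
- **The design is not underpowered or biased without the term.** A reader might infer that precision and protection are lost. The planned 80% is met by an unadjusted calculation, randomisation protects validity, and the test keeps its level. In a logistic model a prognostic covariate can raise power, but it does not shrink the standard error of the odds ratio, and it changes the conditional effect being estimated.
- **Left atrial diameter and continuous PV diameter carry little weight.** Left atrial diameter is recorded (the Protocol amendments section mentions "documentation of LA diameter and LV ejection fraction"), but the article never calls it prognostic, and the 5.5 cm exclusion truncates its range. Replacing the 25 mm cut by a continuous PV diameter gains under 1 point of power in simulation, and it leaves open which vein's diameter would be used.
- **A late change to the primary model has a price.** The trial is open-label and recruitment has ended, so the change could be read as chosen after the fact unless it is clearly dated.

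It can also be said that failure through mere continuation of a drug is a matter of endpoint definition, which no covariate cures. That is true, but the covariate would still deal with a chance imbalance in who enters on a drug.

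**Conclusion.** The point holds as an optional improvement, not as an error or contradiction. The covariate list omits a recorded baseline variable whose link to the endpoint can be read from the article. The consequence is a possible shift of about 1 to 4 points in the success difference at the edge of the 95% range of chance imbalance, and between about 0 and 5 points of unused power. Both ranges rest on assumed prevalence (30% to 70%) and assumed odds ratios (1.5 to 5), because the documents give neither. With an odds ratio of 2 or less there is no power gain, and the shift at that limit stays below 2 points. The documents do not support reading the omission of left atrial diameter, or the PV diameter cut, as a fault.

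**What to change.** Before any unblinded data are seen, add baseline class I/III drug use (yes/no) to the primary logistic mixed model. Take the last record before randomisation: Table 1 allows randomisation up to 10 days before the procedure, so the baseline visit can fall after it. Report the model with the four listed covariates as a sensitivity analysis. Left atrial diameter may be added as well if the sponsor judges it prognostic.

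The cost is one extra model term, an odds ratio conditional on a slightly different set of covariates, and a dated amendment showing that the change preceded unblinding. No new data are needed. If unblinded results have already been seen, leave the primary model as it is and present the added term only as a sensitivity analysis labelled post hoc.
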